## Abstract

**Background:**

Recent research indicates that patients with anorexia (AN) show specific eye movement abnormalities such as shorter prosaccade latencies, more saccade inhibition errors, and increased rate of saccadic intrusions compared to participants without AN. However, it remains unknown whether these abnormal eye movement patterns, which may serve as potential biomarkers and endophenotypes for an early diagnosis and preventive clinical treatments, start to manifest also in people with subclinical eating disorders (ED) symptomatology. Therefore, we propose a protocol for an exploratory experimental study to investigate whether participants with subclinical ED symptomatology and control participants differ in their performance on several eye movement tasks.

**Methods:**

The sample will be recruited through convenience sampling. The Eating Disorder Examination Questionnaire will be administered as a screening tool to split the sample into participants with subclinical ED symptomatology and control participants. A fixation task, prosaccade/antisaccade task, and memory-guided task will be administered to both groups. Additionally, we will measure anxiety and premorbid intelligence as confounding variables. Means comparison, exploratory Pearson's correlations and discriminant analysis will be performed.

**Discussion:**

This study will be the first to elucidate the presence of specific eye movement abnormalities in participants with subclinical ED symptomatology. The results may open opportunities for developing novel diagnostic tools/therapies being helpful to the EDs research community and allied fields.

## Background

Eating disorders (EDs) such as anorexia or bulimia nervosa are a serious problem in our society. They are relatively common, especially among young-adult women [1, 2]; are associated with severe quality-of-life impairments [3], medical and psychopathological comorbidities [4]; have the highest mortality rates of all psychiatric illnesses [5]; and require their own specialized treatments, which results in elevated care costs [6]. Further, EDs are an underestimated problem since a big part of the adult outpatients with EDs do not fully meet DSM criteria [7] and, despite advances in clinical research on EDs, a subset of patients does not improve after receiving treatment [8]. Accordingly, efficacious treatment for EDs is therefore of high importance.

In this context, a vast body of evidence indicates that an earlier diagnosis is considered essential to get more favourable therapeutic outcomes and cost-effective treatments [9–11]. Notwithstanding such advances in prevention research, a challenge reported in ED field is that somatic and psychosocial symptoms, as well as their comorbidities, can be difficult to detect in routine clinical care hindering their preventive treatment [12, 13]. On the other hand, individuals with EDs may fail to report their psychological symptoms [14], experience feelings of stigma and shame about seeking help [15] or have poor insight into perceiving the severity of the illness [14, 16].

To overcome this critical situation, a growing body of literature is focusing on the identification of distinctive biomarkers and endophenotypes associated with EDs [17, 18]. In broad terms, the term biomarkers refers to objectively measured indicators that indicate biological processes [19], while the term endophenotypes refers to quantitative traits in the causal pathway from the genotype to the phenotype [19]. Endophenotypes are distinguished from biomarkers by their causative role. On the contrary, biomarkers are just risk indicators of biological processes and do not play a causal role [19]. Despite their substantive differences, together, biomarkers and endophenotypes offer the potential to improve population-based screens for identifying people who are at risk for psychopathological disorders and can benefit from preventative treatments [20, 21].

While the findings should be interpreted with caution, some authors have speculated that EDs may be linked to a variety of biomarkers and endophenotypes, such as specific metabolic components [22], altered inner body perceptions [23, 24], or neuropsychological weaknesses (e.g., cognitive inflexibility or weak central coherence [25]). More specifically, studies using eye-tracking point out a possible attentional bias linked to disorder-related stimuli, such as food or bodies [26–28]. However, few eye-tracking studies have addressed the role of saccadic eye movements using non-disorder-related procedures (e.g., fixation or pro-/anti-saccade tasks). For example, a recent systematic review of the topic found 28 studies using disorder-related stimuli and only three were involved in the study of saccadic eye movements [28]. Paradoxically, this trend contrasts with the wide body of evidence in psychiatric research that suggests that specific disorders (e.g., depression or schizophrenia) are accompanied by specific patterns of saccadic abnormalities [29, 30]. As a result, in methodological terms, the use of non-disorder-related procedures aimed to identify saccadic eye movement abnormalities is a potential avenue for further research in the ED field. This is because it opens the possibility to provide objective tests and, ultimately, to improve prognostic and preventive treatments, which is an urgent call in the field as previously stated.

In this regard for example, Phillipou et al. [31] found that patients with AN showed poor performance on ocular fixations tasks, i.e., an impaired ability to maintain fixation on a single dot for a longer time compared with control participants. Specifically, they showed an increased rate of saccadic intrusions named square wave jerks (SWJs; these are horizontal, involuntary, saccadic intrusions that interrupt fixation). Recently, Phillipou et al. [32] identified the state independence and heritability of this possible biomarker. According to the results, they found that patients with AN, patients’ weight-restored from the illness, and sisters of people with AN, made significantly more SWJs than healthy controls. Furthermore, the combination of SWJ rate and anxiety showed high accuracy levels to discriminate between the different groups tested (≥ 70%). Another study using prosaccade/antisaccade and memory-guided saccade tasks showed the existence of specific eye movement anomalies in patients with AN [33]. The prosaccade task is stimulus-driven as it requires to perform a saccade (i.e., a ballistic movement of the eyes that shifts the centre of gaze) to an onset peripheral stimulus, a process which is difficult to inhibit. On the contrary, the antisaccade task is goal-driven since it requires volitional processing, a voluntary saccade to the opposite direction of the stimulus. The memory-guided saccade task requires a saccade towards a remembered onset peripheral stimulus after a brief delay. Compared to control participants, patients with AN tended to show shorter saccade latencies in the prosaccade/antisaccade task and more inhibitory errors in the memory-guided saccade task [33].

In sum, the potential clinical value of this research is noteworthy since it may allow screening people at risk of developing AN [18, 34]. The aforementioned research has placed a great focus on clinical and recovered AN samples. Nevertheless, there is a call to focus not only on AN samples, but also including diverse samples such as other ED subtypes [18]. According to this transdiagnostic perspective, it would be possible to find potential biomarkers or endophenotypes to identify "particular symptoms across heterogeneous illness profiles” [18]. In this context, it is not yet known whether these eye movement patterns start to manifest also in heterogeneous samples with subclinical ED symptomatology. Furthermore, studies using subclinical ED samples could help to disentangle a possible influence of starvation (which presumably is less extended under this population than in clinical ED) on these eye-movement patterns and shed light on whether these eye movement abnormalities may be a reflection of the condition itself. On the other hand, given the relative novelty of these results, there is a call in the field to replicate this underpinning research [18, 28], as well as to standardize some of these eye movement tasks (i.e., prosaccade/antisaccade tasks) [35].

### Study objectives and hypothesis

As Malcom and Phillipou [18] noted in their recent review, demonstrating a relationship with illness is one of the first steps in determining biomarkers and endophenotypes. As illustrative example, first Phillipou et al. [33] showed the existence of specific eye movement anomalies in patients with AN and only after these findings, they amplified the scope of their study and were able to identify the state-independence of these eye movement abnormalities [32]. Following this line of reasoning, we will investigate whether the aforementioned eye movement abnormalities detected are, in this case, associated in young-adult women with subclinical symptomatology. Therefore, this study will take as primary aim to investigate whether participants with subclinical ED symptomatology and control participants differ in their performance on a range of eye movement tasks. We hypothesize that participants with subclinical ED symptomatology compared to controls would be prone to show shorter saccade latencies and more inhibitory errors in a prosaccade/antisaccade task and in a memory-guided saccade task, respectively, and an increased rate of SWJs in a fixation task. Additionally, as secondary aim, and following the same approach of Phillipou et al. [31, 32], we will test the potential role of SWJ rate and anxiety for discriminating the different groups tested in our study (participants with subclinical ED symptomatology vs. control participants).

## Methods/design

### Participants and procedure

A young adult female sample will be chosen due to the higher prevalence of EDs in this population [1, 2, 7]. Thus, the sample will comprise young adult women in the 18–25 age range. The sample procedure will be through public advertisements and social media posts (convenience sampling). Inclusion criteria will be: (a) normal (or corrected) visual acuity; (b) gender: women; (c) current body mass index (BMI) in the normal range according to World Health Organization (WHO) (between 18.5–24.9). Exclusion criteria: (a) self-reported lifetime history of significant brain injury, neurological condition, ocular and/or visual pathology; (b) self-reported lifetime history of an ED or other mental illness; (c) self-reported current use of psychotropic drugs (e.g., antidepressants) or intake of recreational synthetic or natural drugs; (d) incomplete data collection or eye-tracker calibration failure; (e) inability to understand Spanish; (f) out of range age. The Spanish Eating Disorder Examination Questionnaire (S-EDE-Q) [36] will be administered since it is considered the gold standard for assessment of ED pathology [37]. The EDE-Q have shown good predictive as well as concurrent validity [37, 38]. Further, has been shown good psychometric properties in young adults in Spain [36]. This tool will serve as a pre-screening tool, allowing us to split the sample into two groups of participants with subclinical ED symptomatology and control participants according to their EDE-Q score, as defined by the study criteria (see below). A global EDE-Q score ≥ 2.8 has been shown to provide an optimal trade-off between sensitivity and specificity when it is used for screening in primary care [38]. The pre-screening will allow to form two groups of similar size: once the desired participant sample size has been reached for one of the groups, only participants falling into the other group defined for the study will be invited to take part.

At the beginning of the experiment a written informed consent will be obtained from all participants. Then, sociodemographic data collection and confounding variables like anxiety and premorbid intelligence quotient (IQ) will be measured. The instructions and questionnaires will be administered by a postgraduate student trained by senior members of the research team. Next, a battery of eye movement tasks presented in the same order will be administered (see the Measures section for more details). After completing the study, a debriefing session will be carried out. The full procedure will take approximately 90 min.

## Measures

### Psychometric measures

#### Eating disorder symptomatology

*Spanish Version of the Eating Disorder Examination Questionnaire (S-EDE-Q)* [36]. Composed by 28 7-point Likert-type response items ranging from 0 (not at all) to 6 points (markedly). Four subscales are measured, including dietary restraint, shape concerns, weight concerns, and eating concerns. The global score ranges from 0 to 6 points. As in Mond et al.’s [37], we will use a cut-off point ≥ 2.8 as clinically significant. Participants will be grouped according to this global index score.

To identify possible confounders, we will explore variables that may affect performance in eye movement tasks (premorbid intelligence and anxiety) [33]. Only those with significant relationships between groups will be deemed potential confounders and included in the analysis.

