### Statistical analysis

Statistical analyses will be performed with SPSS v.28. Normality and outliers will be checked through graphic tests such as QQ plots, histograms, and box plots. Cronbach’s α for each questionnaire will be reported. Group analyses will be performed with Student's t-test paired comparison (for normal distribution) or Wilcoxon tests (for non-normal distribution). We will apply a correction for multiple t-test comparisons. Cohen’s d will be reported for variables showing significance. In case of significant differences between study groups, we will then include confounding variables (premorbid intelligence and anxiety) as covariates in the analysis described above. Across groups, exploratory Pearson's correlation analyses will also be conducted between S-EDE-Q, STAI scores, and BMI and the outcome measures associated with the eye-tracking data (see Table 1, for a detailed view). Additionally, if significant differences are found between STAI scores and SWJ rate, consistent with previous literature [31, 32], a discriminant analysis will be performed on the entire sample to elucidate to what extent both measures correctly classify group membership (participants with subclinical ED symptomatology vs. control participants). Alpha will be set at 0.05 for all analyses.

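### Covariates are admitted only through a significance screen, and the trigger for adding them is ambiguous, which leaves residual bias and can cost power

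*Protocol article*

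**What the plan says.** Two sections of the protocol article set the rule.

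- **Psychometric measures, Eating disorder symptomatology.** Groups are not randomised: "Participants will be grouped according to this global index score". The candidate covariates are chosen for their possible link to the outcome: "we will explore variables that may affect performance in eye movement tasks (premorbid intelligence and anxiety". A second filter follows: "Only those with significant relationships between groups will be deemed potential confounders and included in the analysis".
- **Statistical analysis.** The group comparisons are specified as follows: "Group analyses will be performed with Student's t-test paired comparison (for normal distribution) or Wilcoxon tests (for non-normal distribution". After these, and after a line on reporting Cohen's d, comes the adjustment rule: "In case of significant differences between study groups, we will then include confounding variables (premorbid intelligence and anxiety) as covariates". The covariates are to enter "as covariates in the analysis described above". The section also states: "Alpha will be set at 0.05 for all analyses".

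The Sample size calculation section gives 26 per group for d = 0.8, 80% power and alpha 0.05.

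**The concern.** The groups are split by EDE-Q score in a convenience sample, so imbalance in anxiety or premorbid intelligence is to be expected. Two features of the rule cause trouble.

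1. **Screening by p-value.** The bias that a covariate causes depends on the size of its imbalance and on its correlation with the outcome. Whether its group difference reaches significance depends heavily on sample size as well. With 26 per group, an imbalance large enough to matter will often fail the screen.
2. **An ambiguous trigger.** The condition in Statistical analysis can refer to the eye-movement outcomes or to the covariates. Its position after the outcome tests favours the outcomes; the earlier section favours the covariates. If outcomes are meant, a non-significant comparison is never adjusted, and a difference masked by a confounder stays hidden. The sections also differ on content: one admits only covariates that pass the screen, the other names both without that condition.

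At stake is whether an eye-movement difference, or its absence, can be attributed to ED symptomatology and not to anxiety or premorbid ability. That question is central to a study looking for candidate biomarkers.

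**Working it through.** **Inputs from the protocol article:** 26 per group, d = 0.8, alpha 0.05 (Sample size calculation; Statistical analysis). **Assumptions, because the document gives no figures:** covariate imbalance D in SD units, and within-group covariate-outcome correlation r. Calculations use one covariate, unit within-group SD, two-sided tests and no multiplicity correction.

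**1. The plan's own figure.** A two-sided independent-samples t-test with d = 0.8, alpha 0.05 and 80% power needs n = 25.52, so 26 per group. Power at 26 is 80.7%. The stated sample size reproduces.

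**2. How often the screen catches an imbalance** (noncentral t, 26 per group):

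| True imbalance D | 0.3 | 0.5 | 0.6 | 0.8 | 1.0 |
|---|---|---|---|---|---|
| Flagged | 19% | 42% | 56% | 81% | 94% |
| Missed | 81% | 58% | 44% | 19% | 6% |

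**3. Bias left when the screen misses.** Unadjusted bias is r × (mean imbalance in the studies concerned). At D = 0.5, simulated bias in the missed studies at r = 0.5 is 0.158, which implies a mean imbalance there of 0.158 / 0.5 = 0.316 SD. At r = 0.3 this predicts 0.3 × 0.316 = 0.095; the simulation gave 0.093. Hence about 0.09 to 0.16 SD. ANCOVA with the covariate fixed in advance has bias of about 0.

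**4. Power when the confounder masks a true d = 0.8, with D = 0.5.** The unadjusted test sees d + rD:
- r = -0.3: 0.8 - 0.15 = 0.65
- r = -0.5: 0.8 - 0.25 = 0.55

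A gate on the outcome cannot do better than the unadjusted test. ANCOVA works with d / [sqrt(1 - r²) × sqrt(VIF)], where VIF = 1 + D²/4 = 1.0625 and its root is 1.031:
- r = -0.3: 0.8 / (0.954 × 1.031) = 0.81
- r = -0.5: 0.8 / (0.866 × 1.031) = 0.90

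Simulated power:

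| | r = -0.3 | r = -0.5 |
|---|---|---|
| Trigger is the outcome (gate) | 63% | 50% |
| Trigger is the covariate (screen alone) | 74% | 73% |
| ANCOVA fixed in advance | 81% | 88% |

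**5. False positives with no true effect** (simulated). "Screen plus gate" counts a positive if the unadjusted test is significant and, where the covariate was selected, the adjusted test is too.

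| D, r | Unadjusted | Screen alone | Screen plus gate |
|---|---|---|---|
| 0.5, 0.3 | 8% | 5% | 4% |
| 0.5, 0.5 | 14% | 6% | 5% |
| 0.8, 0.5 | 29% | 6% | 4% |

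**6. Precision from a balanced covariate.** Power for d = 0.8 with ANCOVA rises from about 81% to about 83-84% at r = 0.3, and to 90% at r = 0.5. The screen would select such a covariate only about 5% of the time, so the plan forgoes nearly all of this gain.

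**7. Cost of adjusting.** If STAI differs by D = 1.0, the group-STAI correlation is 1/sqrt(5) = 0.447, VIF is 1 / (1 - 0.2) = 1.25, and the SE rises by a factor sqrt(1.25) = 1.118, before any fall in residual variance.

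**The case against.** A fair defence has several parts.

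- **The outcome link is not ignored.** A reader might infer that covariates are chosen on group imbalance alone. The text does not support this: candidates are first limited to variables thought to affect task performance. The weakness lies in the second filter.
- **The rule controls false positives.** One might expect confounded positives to pass through. In the scenarios run, rejection under the null after the rule stayed at about 3% to 6%, although the unadjusted test alone rejected far more often. This part of the defence stands.
- **Large imbalances are caught.** At D = 1.0 the screen flags the covariate 94% of the time. With r = -0.3 and d = 0.8, the screen alone gives 74% power against 75% for ANCOVA. The fall to about 42% arises only under the outcome gate, so it is no evidence against the screen. Nor can it be said without condition that masked differences stay hidden; that depends on which trigger is meant.
- **A t-test or Wilcoxon test takes no covariate.** One might conclude that the adjusted analysis cannot be run. Adding covariates to a comparison of two means ordinarily means ANCOVA, and a condensed article may leave the model's name to the full plan. This carries little weight.
- **Anxiety may belong to the ED profile.** It is a discriminating variable in the secondary aim, so an adjusted estimate should not replace the unadjusted one. This stands and shapes the fix.
- **The study is exploratory**, and checking whether significant differences survive adjustment is coherent. That does not justify leaving null results unadjusted or discarding a covariate because its own test was not significant.

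**Conclusion.** The point holds for the significance screen and for the unreconciled trigger. The screen misses a 0.5 SD imbalance 58% of the time and a 0.3 SD imbalance 81% of the time; these figures need only the stated sample size and a two-sided 0.05 test. The consequences rest on assumed correlations. Bias is about 0.09 to 0.16 SD in the missed 0.5 SD cases for r = 0.3 to 0.5. Where a confounder opposes the effect, the power loss against ANCOVA is 81 - 63 = 18 to 88 - 50 = 38 points if the trigger is the outcome, and 81 - 74 = 7 to 88 - 73 = 15 points if it is the covariate. Weaker correlations shrink all of these. The planned multiplicity correction would lower the absolute powers.

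Two stronger conclusions are not supported. The rule does not inflate the final false-positive rate in any material way. Nor is the lost precision always large: it is about 3 points of power at r = 0.3 and 9 at r = 0.5. This should be changed, but it does not invalidate the study.

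**What to change.** Delete the significance screen in the Eating disorder symptomatology section and the conditional entry in Statistical analysis, and replace both with one rule:

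- For each hypothesised outcome, report the unadjusted group comparison and a pre-specified ANCOVA with group, Word Accentuation Test score and one STAI score (state or trait, named in advance), whatever the p-values.
- If an outcome is skewed, transform it or use a rank-based ANCOVA.
- Interpret the anxiety-adjusted estimate beside the unadjusted one, stating that anxiety may be part of the ED profile.

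The cost is one extra model per outcome, using data already to be collected. If STAI differs by 1.0 SD between groups, the adjusted SE is about 12% larger before any gain from lower residual variance.

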#### Premorbid intelligence

*The Word Accentuation Test* [39]. Composed by 30 low frequency Spanish words whose accents have been removed. Participants must demonstrate their knowledge of the correct accentuation of each word. The total score is the number of words correctly read (from 0 to 30). The test is administered individually and takes 2–3 min.

